The main objective of this study is to examine the differential effects of a Mindfulness-Based Health Care Program (MBHC) without versus with VR-assisted meditation (MBHC-VR) on OB and mental health (i.e. psychological distress) in university students. Our seven objectives are:

To compare the training effects on occupational indicators, such as occupational balance, eating habits, sleep and physical activity.To compare the training effects on mental health indicators, such as anxiety, depression, stress and burnout.To compare the training effects on psychological functioning, such as emotional regulation, acceptance, mindfulness-trait, self-compassion and life satisfaction.To test whether the training effects are maintained 3 months post-completion of MBHC.To identify potential mechanisms of change in MBHC vs MBHC-VR.To examine expectations of the participants before their participation in the program.To qualitatively explore the perceptions of the participants about the program and its effects after its completion.

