### Participants

Participants will be bachelor degree, masters, or doctorate students at Miguel Hernández University of Elche. Recruitment will be carried out over two academic years. Invitations to participate will be disseminated by institutional mailings, university’s official website, informative posters, and dissemination talks. Students interested in participating will, voluntarily pre-enroll by completing a brief online questionnaire on contact information, eligibility criteria, previous experience in meditation, and program expectations.

Inclusion criteria include: a) being 18 years old or older; b) enrolled in a bachelor degree, master or doctorate degree program at Miguel Hernández University of Elche; c) speak Spanish fluently; d) signing the Informed Consent form; and g) having internet access from a computer or smartphone to complete the online assessments and formal practices during the study. Furthermore, participants will be excluded if they: a) report a severe mental disorder in active phase diagnosed by a health professional (e.g., schizophrenia, bipolar disorder, substance abuse/dependence); b) are under the influence of alcohol or other drugs during sessions and/or assessments (determined by the program instructor); and c) participate in another standardized meditation program during the study period. Should any participants require psychological or psychiatric treatment during the study, they will be referred to specialized care services.

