### Randomization, allocation and blinding

Participants who satisfy eligibility criteria will be randomly assigned to one of the three intervention groups in a ratio of 1:1:1 using the randomize R package in R [39]. Randomization will be performed after the baseline assessment to preserve allocation concealment.

The participants will be randomly assigned to the MBHC, MBHC-VR or WL and informed by telephone one week before starting intervention or WL groups. Fig 1 summarizes the flowchart of the study.

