#### Waiting list control group (WL)

Participants in the WL control group will not receive any intervention during the study. However, for ethical reasons, at the end of the 3-month follow-up assessment, participants of this WL control group will be invited to participate in the MBHC program free of charge.

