### Adverse events and safety considerations

The scientific literature on meditation-associated adverse events [MRAEs] is sparse and contradictory. However, some recent studies have suggested that MRAEs do occur in these meditation-based interventions, including those that focus on mindfulness [61–63]. According to a recent meta-analysis [64], the prevalence of MRAEs in experimental studies is 3.7% (95% CI = 0.02–0.05). The most frequent MRAEs were anxiety, depression and cognitive abnormalities (e.g. thought disorganization), stress and hallucinations and, normally, they appeared during or immediately after the practice [64].

On the other hand, regarding VR, scientific evidence shows disorientation followed by nausea and oculomotor disturbances as the most frequent negative effects, although their magnitude seems to be conditioned by factors such as the socio-demographic characteristics of the users, the VR content (neutral versus exciting) and the exposure time (adaptation after repeated exposures and greater orientation in exposures equal to or greater than 10 minutes) [65].

In this clinical trial, the participants will be encouraged to report any adverse events occurring during practice as soon as possible by WhatsApp or in-person during class. Any adverse events will be reported by the principal investigator to the Research Ethics and Integrity Committee of the Miguel Hernández University using an adverse event report. Additionally, should any participants require psychological or psychiatric treatment during the study, they will be excluded and referred to specialized care services.

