### Data analysis

#### Quantitative data analysis plan

The data analysis plan will be conducted following four steps. R Software [66] will be used for all data cleaning and statistical tests with a significance level of alpha < .05.

*Data preprocessing*. Demographics and clinical records will be described at baseline by means of frequencies (percentages) or means (SD). Independent *t*-test for continuous data and chi-square test (*χ*^2^) for categorical data will be conducted to confirm that there were no demographic or clinical differences between groups at baseline. Following the CONSORT guidelines [38], Intention-To-Treat analysis will be performed using Maximum Likelihood estimation via Expectation Maximization imputation [67]. The procedure suggested by Hair et al [68] will be followed to handle missing data: 1) the types of missing data and percentage of missing will be analyzed to ensure that none exceed the recommended thresholds; 2) Little’s MCAR (Missing Completely At Random) test will be used to assess whether the missing data is completely random; and 3) sensitivity analysis will be performed to determine the impact of missing data on the results of a study, comparing the main outcomes between completers and imputed values.

*Multilevel Modelling (MLM)*. First, efficacy of MBHC and MBHC-VR compared to WL control condition will be analyzed by using MLM. Multilevel analysis enables the control of variance associated with random factors without the need for data aggregation. Variance across participants, instructor of each group, and subgroup of delivery (i.e., edition) will be modeled as random effects. Group (i.e., MBHC, MBHC-VR, and WL) and time (i.e., pre-intervention, inter-session, post-intervention, and 3-month follow-up) will be modeled as fixed effects. Analyses will be conducted via restricted maximum likelihood estimation (REML), which provides a less biased estimate of variance components with small sample sizes [69]. The group x time interaction will be used to study the trajectories of each group throughout the intervention and to determine whether the between-group differences are maintained over time.

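### The protocol says both that participants who need mental-health treatment during the study are excluded and that they are only referred, and does not keep them in the intention-to-treat data.

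*Protocol article*

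**What the plan says.** Two sections of the protocol article give different rules for one event. Under Adverse events and safety considerations: "should any participants require psychological or psychiatric treatment during the study, they will be excluded and referred to specialized care services". Under Participants: "Should any participants require psychological or psychiatric treatment during the study, they will be referred to specialized care services". The Discussion also mentions referral, where necessary, and no exclusion.

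The Participants section lists two exclusion criteria that can be met while the study is running. Criterion (b) covers people who "are under the influence of alcohol or other drugs during sessions and/or assessments (determined by the program instructor". Criterion (c) covers people who "participate in another standardized meditation program during the study period".

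On timing, Randomization, allocation and blinding says "Randomization will be performed after the baseline assessment to preserve allocation concealment", and participants learn their arm one week before the start. On the analysis, the Quantitative data analysis plan says "Intention-To-Treat analysis will be performed using Maximum Likelihood estimation via Expectation Maximization imputation".

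The main objective concerns effects "on OB and mental health (i.e. psychological distress) in university students", and Table 1 lists DASS-21 anxiety, depression and stress among the main outcomes. For the control arm: "Participants in the WL control group will not receive any intervention during the study".

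**The concern.** Study staff cannot follow both sections: one excludes the participant and the other does not. The difference matters because exclusion would mostly happen after randomisation, for a reason close to what the trial measures. A student who comes to need psychological or psychiatric care is likely to have high distress scores. If that student's later outcomes are not collected, or the student is left out of the analysis, the arm's mean distress looks better than it was.

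The loss may also differ by arm. The safety section asks for reports of adverse events that arise in practice, sent by WhatsApp or given in class. The waiting list has no class and no assigned practice, so deterioration may be noticed more readily in the two active arms. On the other hand, waiting-list students receive no intervention and might need care more often. The sign of any bias therefore cannot be settled from the document.

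**Working it through.** **1. Sequence of events.** Baseline assessment, then randomisation, then six weeks of programme or waiting, then post-intervention assessment and three-month follow-up. An event during the study that leads to treatment will mostly fall after randomisation.

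**2. What exclusion covers.** No section limits it to stopping sessions, and none says that an excluded participant still receives questionnaires or stays in the analysis set. The Discussion plans to call back people who miss the post-intervention assessment. That addresses non-attendance and says nothing about excluded participants.

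**3. Whether imputation repairs it.** EM imputation is valid if, given the observed data, missingness does not depend on the unseen values. That is doubtful when removal follows a worsening between assessments. The planned sensitivity analysis compares completers with imputed values, and neither set contains the scores that excluded participants would have given.

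**4. The listed exclusion criteria.** Criterion (b) is judged by the instructor. It names assessments as well as sessions, but the assessments are described as online, where an instructor sees nobody. In practice it works in sessions, which only the active arms have. Criterion (c) can be checked at the telephone eligibility interview as current or planned enrolment. It raises the concern only if applied after enrolment.

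**5. Size, as an illustration.** The protocol states no exclusion rate, so there is no figure of the plan's to reproduce. Assumptions: outcome normal with SD 1, no true difference between arms, and removal of the fraction p with the highest value of a variable that correlates r with the outcome. Removed people are dropped, with no help from baseline scores or imputation. The mean of those who remain shifts by

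r × φ(z) / (1 − p), where z is the upper-p normal quantile and φ the normal density.

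At r = 1:
- p = 0.02: 0.0484 / 0.98 = 0.049 SD
- p = 0.037: 0.0809 / 0.963 = 0.084 SD
- p = 0.05: 0.1031 / 0.95 = 0.109 SD

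Spurious difference between two arms, for r from 0.5 to 1:

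| Removed, one arm vs other | r = 0.5 | r = 1 |
|---|---|---|
| 3.7% vs 0% | 0.042 | 0.084 |
| 5% vs 2% | 0.030 | 0.059 |
| 3.7% vs 3.7% | 0 | 0 |

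A simulation of the same set-up gave 0.045 to 0.083 SD for the first row and about 0.03 to 0.06 SD for the second, which agrees within simulation error. The rate of 3.7% is borrowed from the prevalence of meditation-related adverse events that the safety section cites. It is not a rate of needing treatment. At that rate, 70 × 0.037 = 2.6 participants per arm would be affected.

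**The case against.** The strongest reply is that exclusion appears in a safety section and may mean leaving the programme only. Baseline scores precede randomisation, the plan promises intention-to-treat with imputation, and the call-back plan shows a wish to keep collecting data. This stands in part. A reader might infer that the protocol orders the deletion of these people from the efficacy data, in open breach of intention-to-treat. It does not say so. What it does is give two rules for one event and leave the reach of the stricter one open.

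Three further stronger readings are not supported:
- **Both behaviour criteria as post-randomisation exclusions.** They stand in an eligibility list, and eligibility is confirmed by telephone before enrolment. Criterion (b) is hard to apply before sessions begin, but criterion (c) is not. That waiting-list members would join another programme more often is conjecture.
- **Removal on the outcome itself.** Need for treatment is not a DASS-21 score. Occupational balance, academic stress and burnout are also main outcomes and are tied to it less directly.
- **A bias that is a large share of the planned effect.** The design value of d² = .08 (d = 0.28) refers to the programme with against without VR. Those arms share content and instructors, so one-sided exclusion is least plausible there. No planned effect is given for the contrasts with the waiting list. Rates such as 10% have no basis in the document, whose quoted interval for adverse events is 0.02 to 0.05.

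**Conclusion.** The concern holds as a conflict within the protocol that carries a risk of bias; bias is not demonstrated. The safety and Participants sections disagree on whether a participant who needs treatment is excluded. If exclusion extends to follow-up or analysis, it is at odds with intention-to-treat and causes outcome-related loss after randomisation that the planned imputation would not reliably correct. Criterion (b) carries the same risk if used after randomisation. Criterion (c) does so only if used after enrolment.

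Under the assumptions shown, the distortion is a few hundredths of an SD, up to about 0.08 SD in the scenarios tabulated. It vanishes when removal is equal and equally selective in the arms compared. Its direction is unknown. The contradiction needs correcting whatever the size, because outcomes that were never collected cannot be recovered in analysis.

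**What to change.** Reconcile the Participants and safety sections so that one rule is stated. Add that, whatever is decided about a participant's care or further sessions, these events do not remove a randomised participant from outcome collection or from the intention-to-treat analysis. Apply the listed exclusion criteria as eligibility criteria before randomisation. Record later events (treatment started, intoxication noted, another programme joined) by arm. No clinical rule is proposed here; care and continued attendance remain for the investigators to settle.

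The cost is protocol wording and a few more online questionnaires to people already enrolled.

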### Data analysis

#### Quantitative data analysis plan

The data analysis plan will be conducted following four steps. R Software [66] will be used for all data cleaning and statistical tests with a significance level of alpha < .05.

*Data preprocessing*. Demographics and clinical records will be described at baseline by means of frequencies (percentages) or means (SD). Independent *t*-test for continuous data and chi-square test (*χ*^2^) for categorical data will be conducted to confirm that there were no demographic or clinical differences between groups at baseline. Following the CONSORT guidelines [38], Intention-To-Treat analysis will be performed using Maximum Likelihood estimation via Expectation Maximization imputation [67]. The procedure suggested by Hair et al [68] will be followed to handle missing data: 1) the types of missing data and percentage of missing will be analyzed to ensure that none exceed the recommended thresholds; 2) Little’s MCAR (Missing Completely At Random) test will be used to assess whether the missing data is completely random; and 3) sensitivity analysis will be performed to determine the impact of missing data on the results of a study, comparing the main outcomes between completers and imputed values.

*Multilevel Modelling (MLM)*. First, efficacy of MBHC and MBHC-VR compared to WL control condition will be analyzed by using MLM. Multilevel analysis enables the control of variance associated with random factors without the need for data aggregation. Variance across participants, instructor of each group, and subgroup of delivery (i.e., edition) will be modeled as random effects. Group (i.e., MBHC, MBHC-VR, and WL) and time (i.e., pre-intervention, inter-session, post-intervention, and 3-month follow-up) will be modeled as fixed effects. Analyses will be conducted via restricted maximum likelihood estimation (REML), which provides a less biased estimate of variance components with small sample sizes [69]. The group x time interaction will be used to study the trajectories of each group throughout the intervention and to determine whether the between-group differences are maintained over time.

P-values will be obtained through likelihood ratio tests comparing the full model (including the effect in question) with the model that excludes this effect. Z-values will be obtained to test the significance for fixed effects (estimates and standard errors data in the tables). Trends of the longitudinal data will be studied by testing the linear trend of the model for all the outcomes. Interaction effects between time and predictors will be performed. To estimate the magnitude of between-group differences at post-intervention and 3-month follow-up, effect sizes (Cohen’s *d*) will be calculated by dividing the differences in means by the pooled standard deviation (SD). The Cohen convention was used to interpret effect sizes, where effect sizes of 0.20 are categorized as small, effect sizes of 0.50 are classified as medium, and effect sizes greater than or equal to 0.80 are considered large.

Model comparison approach will follow Bliese and Ployhart [70] and Bliese [71] guidelines. The process begins by examining the nature of the outcome. To test the significance of person effects, a likelihood ratio test will be conducted to compare the null multilevel model (i.e., unconditional model) with a null single-level model, testing the null hypothesis that there are no group differences. The second step involves estimating the intraclass correlation coefficient (ICC) to calculate the between/within variation ratio. Model fit will be assessed using chi-square tests on the log-likelihood values and the Akaike’s information criterion (AIC) [72] relative goodness of fit index. According to the change in these fit indexes, the model with the last significant change will be chosen for each analysis.

MLM will be performed using the lme4 R package [73]. P-values of the lme4 outputs will be obtained by the lmerTest R package [74]. The Intraclass Correlation Coefficient (ICC) will be calculated by the sjstats R package [75]. Graphic data processing will be performed by the ggplot2 R package [76]. Visual inspection of q-q plots by the car R package [77] will reveal any deviations from homoscedasticity or normality in the dependent variables. In order to calculate multiple comparisons, Tukey/Bonferroni correction tests will be performed.

*Structural equation model (SEM)*. We will use the lavaan R package to implement structural equation models (SEM) by to investigate whether there are any significant mediators of training outcome. Results will be reported following the recommendations in Raykov et al. [78]. Cases with missing values and outliers will be detected using Mahalanobis distance. Multivariate and univariate normality assumptions will be tested using Mardia’s test and Kolmogorov-Smirnov’s test with the MVN R package [79]. If non-normality is found, Satorra-Bentler scale test and standard bootstrapping will be used. Model fit will be assessed using several criteria [80]: 1) a ratio of *χ*^2^*/gl<2* suggests an acceptable fit; 2) A RMSEA size below .06 suggests a well-fitting model; 3) a comparative fit index (CFI) above .95 indicates a good fit; 4) a SRMR of less than .09 also indicates a good fit; and 5) The chi-square statistic provides a conventional measure of model fit.

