### Sample size estimation

G *Power (v. 3.1) was used to estimate the sample size needed to test hypotheses 1, 2, 3 and 5. A mixed model using treatment as a between-subjects factor (MBHC, MBHC-VR, and WL) and time as a within-subjects factor (pre, inter, post, and follow-up) will be tested. Interaction effect was powered. The sample size was estimated taking as a reference a small difference in perceived stress between MBHC with vs without VR-assisted meditation in university students [5]. With an alpha criterion of .05 and a small effect size (Cohen’s d^2^ = .08), to achieve a minimum of 80% power, a minimum sample size of 174 participants will be needed. Assuming an attrition rate, based on complete dropout of approximately 20% [5], the final sample needed will include at least 210 university students (i.e., 70 participants in each of three groups).

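### Baseline significance tests cannot confirm balance, and a common baseline mean with baseline-adjusted effect sizes would make better use of the same data

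*Protocol article*

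**What the plan says.** Under the quantitative data analysis plan (data preprocessing), the protocol article first describes the arms with percentages or means and SDs. It then specifies an independent t-test "for continuous data and chi-square test" for categorical data. These tests "will be conducted to confirm that there were no demographic or clinical differences between groups at baseline". The general rule is that R "will be used for all data cleaning and statistical tests with a significance level of alpha < .05".

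The randomisation section places allocation after the baseline assessment, 1:1:1 to three arms.

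The multilevel model has group, time and their interaction as fixed effects, and pre-intervention is one of the levels of time. No equal-baseline constraint and no baseline covariate is stated. Between-group effect sizes at post-intervention and 3-month follow-up "will be calculated by dividing the differences in means by the pooled standard deviation (SD"), and are then labelled against 0.20, 0.50 and 0.80.

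**The concern.** The plan draws a conclusion of no difference from p > .05, with no margin. After randomisation the null hypothesis of these tests is true by design if allocation was sound. A significant result is then a chance finding, and a non-significant one says little about how close the arms are. The named t-test also compares two groups while the trial has three, so it needs three comparisons per variable.

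What matters more is how the analysis treats chance imbalance. A model with a separate baseline mean per arm does not use the fact that randomisation makes those means equal in expectation, and so gives up precision. An effect size built from post-intervention or follow-up means alone carries part of any baseline gap. It can therefore tell a different story from the group-by-time test, which is measured from baseline.

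**Working it through.** **Inputs from the protocol article.** Alpha .05 (sidedness not stated; two-sided assumed). Sample size: "at least 210 university students (i.e., 70 participants in each of three groups"), after about 20% dropout, so 70 × 0.8 = 56 per arm with data. Sizing effect: "a small effect size (Cohen’s d^2^ = .08"), so d = √.08 = 0.283. Table 1 marks 22 variables at pre-intervention: 6 main, 10 secondary and 6 sociodemographic (17 continuous and 5 categorical by my count). **Assumed, not in the document:** the pre–post correlation rho, the correlation between baseline variables, and equal SDs over time.

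**The plan's own figure.** The article says that "to achieve a minimum of 80% power, a minimum sample size of 174 participants will be needed". For a 3 × 4 interaction, lambda = f²·N·m/(1 − rho) with df 6 and 3(N − 3). At N = 174, power is 0.804 with f = .10 and rho = .5, and also 0.804 with f = d/2 = .141 and rho = 0. The stated number is reproduced, but the article does not say which reading was used. I therefore use 0.28 SD below only as an illustrative size.

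**What the baseline test lets through.** The smallest observed difference flagged at 70 per arm is t(.975, 138) × √(2/70) = 1.977 × 0.169 = 0.334 SD. Everything smaller passes. An observed 0.283 SD gives p = .097.

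**How often it flags chance.** One continuous variable tested over three pairs gives at least one p < .05 in 12.1% of sound randomisations. Simulated over all 22 variables (3 × 70 participants, no true differences, no multiplicity correction, categorical variables simulated as independent binaries):

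| Correlation among continuous variables | All tests pairwise | One three-group chi-square per categorical variable |
|---|---|---|
| 0 | 95% | 91% |
| 0.3 | 91% | 86% |
| 0.5 | 85% | 76% |
| 0.7 | 75% | 64% |

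Bonferroni within each variable would lower the pairwise column to 39–61%. Testing only the six main outcomes pairwise gives 38–55%.

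**How imbalance reaches d.** Given an observed baseline gap of δ SD, the expected shift in the unadjusted post-intervention difference is rho × δ. For a gap just passing the check (0.33 SD), the shift is about 0.17 at rho = 0.5 and 0.23 at rho = 0.7. That is comparable to the 0.20 the article uses as its small-effect benchmark. The pre-to-post change contrast shifts by (rho − 1) × δ, in the opposite direction, so the two can disagree in one realised trial. Averaged over randomisations, both shifts are zero.

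**Precision lost.** In units of 2σ²/n, the variance of the pre-to-post contrast is 2(1 − rho) with free baseline means and 1 − rho² with a common baseline mean or baseline covariate. The ratio is (1 + rho)/2:
- rho = 0.5: 1.00 against 0.75, a 25% reduction.
- rho = 0.7: 0.60 against 0.51, a 15% reduction.

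Power per contrast at 56 per arm uses noncentrality effect × √(56/2) / √(variance term), critical value 1.98:
- 0.28 SD, rho = 0.5: 1.50 against 1.73, power 32% against 40%.
- 0.28 SD, rho = 0.7: 1.93 against 2.10, power 48% against 55%.
- 0.5 SD, rho = 0.5: 2.65 against 3.06, power 75% against 86%.
- 0.5 SD, rho = 0.7: 3.42 against 3.70, power 92% against 96%.

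**The case against.** The best case for the plan is that nothing depends on these tests. The article sets no gate, no covariate selection and no change of model on their result. Efficacy rests on the group-by-time interaction, which is measured from baseline and is not biased. An unconstrained longitudinal model is valid and widely used. All of that stands, and it limits the point to a misplaced inference plus an inefficient and inconsistent summary.

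The effect-size sentence does not say whether the means are raw or model-estimated, and a condensed article may leave that to the full plan. This helps only in part. With complete data, a model with free baseline means returns essentially the raw post-intervention means, so model-based means would carry the same imbalance.

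A reader might go further and infer that the check is dangerous because it has only 38% power, and so misses 62%, at a baseline difference of 0.283 SD with 70 per arm. The arithmetic is right, but it assumes a true baseline difference, which sound randomisation excludes. What matters is the observed imbalance, and there the test simply cuts at 0.334 SD. Nor does the article establish 0.283 as the pairwise effect it was sized on, since it powered the interaction.

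A reader might also infer that the tests replace baseline adjustment or will choose covariates. The article says neither.

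**Conclusion.** The point holds in a limited form. Using non-significance to confirm balance is unsound, and on most readings of the plan at least one chance flag is more likely than not. The 64–95% range is not a document figure: it rests on 22 variables, uncorrected tests and assumed correlations of 0 to 0.7, and correction or a shorter list of variables would lower it.

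The efficacy test is not invalidated. The practical loss is precision (a 15–25% smaller variance of the pre-to-post contrast is available if rho is 0.5–0.7) and an effect size that can move by about rho times a chance baseline gap. The power gain is modest: 7 to 8 percentage points at 0.28 SD, and 4 to 11 points at 0.5 SD, over the same range of rho. This is an improvement worth making rather than a flaw that undermines the trial.

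**What to change.** - Delete the baseline significance tests and keep the descriptive table already planned, adding standardised differences if wanted.
- In the multilevel model, constrain the baseline mean to be equal across the three arms. Alternatively, use the baseline score as a covariate with post-intervention and follow-up as the outcomes.
- Compute Cohen's d from these baseline-adjusted contrasts divided by the baseline SD, so that the effect size and the test describe the same quantity.

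The cost is a few sentences in the analysis plan and one change to the model formula. No new data are needed, since the baseline scores are already collected. The change should be fixed before outcome data are examined.
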